## Methods

### Setting/sites

ACCESS Open Minds’ 14 sites represent pan-Canadian variations in geography, culture, resources, and population density [30] (see Table 1). Together, they serve youth in urban, rural, and remote communities; non-Indigenous and Indigenous youth; Anglophone and Francophone youth; and groups with particular vulnerabilities (immigrants, refugees, ethnic minorities, state-protected youth, homeless youth, and first-year university students). Ten sites cover specified catchment areas, strengthening the representativeness of the youth populations they serve.

**Table 1 Tab1:** ACCESS Open Minds Site Descriptions (A list of study sites with addresses can be obtained from the trial registry)

Site (prominent languages of the milieu)	Province	Youth Population^1^	Target N of youth expected to consent to research^2^	Notable features of youth population, if any	Service system features
URBAN SITES					
PEER Saint John (English)	New Brunswick	11,085	277	Many low socio-economic status, many NEET^3^	Mental health day-treatment centre
Dorval-Lachine- Lasalle (French, English)	Québec	18,530	864	28% speak languages other than English/French	Primary care centre offering health and social services to specified geographic catchment
RIPAJ-Montréal Homeless Youth Network* (French, English)	Québec	1000*	93	Homeless, many NEET	Network of community organisations; and primary and tertiary public health and social service settings
Parc-Extension (English, French)	Québec	5065	236	Large numbers (over 60%) are visible minority and immigrant	Primary care centre offering health and social services to specified geographic catchment
Edmonton (English)	Alberta	17,010	700	Many homeless, Many NEET	Governed by single authority that provides health care to entire province
University of Alberta* (English)	Alberta	8000	329	First year university students	Student services at the university
SEMI-URBAN / RURAL					
Caraquet, Acadian Peninsula (French)	New Brunswick	555	39		Mobile team and community centre
Chatham-Kent (English)	Ontario	17,355	865	Also serves two neighboring First-Nation communities	Community-based youth services hub; Key partners are public health and addictions program and a community mental health organization.
INDIGENOUS / REMOTE					
Eskasoni First Nation (Mi’kmaq, English)	Nova Scotia	1025	–		Mental health centre (division of health centre) accountable to the Band Council
Elsipogtog First Nation (Mi’kmaq, English)	New Brunswick	839	–		Health centre and youth space accountable to the Band Council
Cree Nation of Mistissini (Cree, English)	Québec	1015	–		Network of services funded by Cree Health Board and local Band Council
Puvirnituq (Inuktitut, English)	Québec	535	–	Remote, Northern	Lay health workers in collaboration with Saqijuq, a community youth diversion initiative
Sturgeon Lake First Nation (Plains Cree, English)	Saskatchewan	350	–		Youth Space with mobile ACCESS clinician services
Ulukhaktok (Inuvialuit, English)	Northwest Territories	105	–	Remote, Northern	Lay health workers in collaboration with Inuvialuit Regional Corporation^4^

^1^Based on estimate for number of youth aged 10 to 24 from the Census Profile, 2016 Census, Statistics Canada ^2^ This column represents the expected number of youth who will consent to research at each site. This number represents 60% of the total number of youth who are projected to receive services at each site. This projected number was arrived at using each site’s known youth population and estimates of youth mental health help-seeking prevalence and unmet needs from the Canadian Community Health Survey – Mental Health (CCHS-MH; 2012). Although Indigenous communities had not been included in the CCHS-MH, the same formula was used to arrive at minimum target numbers for the Indigenous community sites, knowing that these would be under-estimates given the expected higher prevalence of mental health help-seeking in Indigenous contexts. These minimum estimates for Eskasoni First Nation, Elsipogtog First Nation, Cree Nation of Mistissini, Puvirnituq, Sturgeon Lake First Nation and Ulukhaktok were 68, 56, 44, 23, 17 and 5, respectively. The CCHS-MH based formula was also not used for RIPAJ and University of Alberta (marked with *) which are not catchment-area based sites. ^3^ NEET = Not in employment, education or training ^4^ Inuvialuit Regional Corporation (IRC) is an Indigenous Organization currently under-going self-government negotiations. IRC does not directly deliver mental health services in the Inuvialuit Settlement Region but delivers many social, wellness and cultural programs that supplement services provided by the Government of Northwest Territories

Six sites are in Indigenous communities, where populations tend to be young [32]. In some Indigenous communities, youth are reported to have very high rates of suicidality, addiction, violence, school drop-out, unemployment, and involvement with justice and youth protection systems [33]. It has been proposed that these problems stem from and are compounded by the cultural fragmentation and inter-generational trauma inflicted by brutal colonial and government policies [34]. The situation is exacerbated by varying combinations of geographic isolation (e.g., two sites are only accessible by air and boat); poverty; the inadequacy of health and psychosocial services and associated funding; and service providers’ unfamiliarity with local histories, languages and contexts [35].

### Study intervention

At each site, the ACCESS Open Minds “intervention” transforms services [21, 22] to provide:
*Early case identification* through targeted outreach, community awareness, etc., so that more youth self-refer or are referred sooner (see online early identification guide) [36].*Rapid, engaging access*, offering an initial evaluation within 72 h in a non-emergency, community-based environment. To this end, a trained “ACCESS Clinician” is deployed to conduct initial evaluations; involve family members in assessment; and link youth with services tailored to their needs and preferences. Rapidity is also ensured through the plurality of portals of access, including direct walk-in; the elimination of referral or administrative requirements; and the use, where appropriate, of technologies like social media, helplines, etc.*Appropriate care* in the form of evidence-informed, illness-appropriate interventions offered within 30 days of initial evaluation (per Canadian Psychiatric Association benchmarks) [31]. Because youth can present with non-specific, overlapping symptoms, treatment planning is guided by youths’ self-reported distress and social-vocational functioning and clinicians’ impressions of problem severity, rather than specific diagnoses. Provided in youth-friendly, non-stigmatizing, and recovery-oriented environments, care is focused on youth’s own goals. Where appropriate interventions are unavailable, site staff connect youth to external services/specialists.*Continuity of care*, to ensure that youth receive appropriate care for as long as needed. This is achieved by fostering collaboration between services, stakeholders, sectors, and disciplines to eliminate jarring age-based transitions and to reduce or smoothen transitions between other services youth need, e.g., from primary to specialized care.*Youth and family/carers engagement*, to ensure their active involvement, in keeping with the SPOR vision of valuing lived experience. This entails including youth and families in network- and site-level service design, oversight, and hiring committees; seeking their inputs in designing youth spaces; offering individualized menus of interventions, flexible appointment times and, when possible, choices of treatment venues; and training clinicians in youth-friendly, strengths-affirming approaches.

At all sites, transformation began with a community mapping [37–39] exercise that identified, linked up and, where possible, co-located all youth-focused resources in the community (see online guide) [40]. Additional capacity was integrated through hiring an ACCESS Clinician and other requisite staff, training, and external partnerships (e.g., with the national helpline, Kids Help Phone). Additional details about the model and its operationalization appear in our prior open-access publication [30].

Although a dynamic process, service transformation is deemed to commence at each site with: (a) the finalization of a site-specific service transformation plan (on the basis of which a contract is signed and funds are allocated) with clear activities outlined to achieve each service objective; (b) the deployment of the ACCESS Clinician; and (c) the training of key site staff in ACCESS Open Minds principles and evaluation protocols.

Core strategies common to all sites’ transformation plans include deploying an ACCESS Clinician; responding to help-seeking/referrals within 72 h; and creating a youth-friendly physical space. Relevant evidence and local conditions inform additional site-specific strategies. For instance, twice-yearly early identification activities may target all youth at sparsely populated Indigenous sites, but only potential referral sources (e.g., schools) at more populous urban sites. The relevance, acceptance and ownership of each site’s service transformation plan are assured through broad stakeholder engagement.

### Study design

The impact of ACCESS Open Minds is being evaluated using a multi-method design that includes a minimum evaluation protocol at all sites, and a stepped-wedge cluster randomized trial at six sites.

*Minimum evaluation protocol*: Our minimum evaluation protocol — developed collaboratively in consultation with youth, families, researchers, and clinicians — is designed to collect data that address our primary and secondary hypotheses (see Table 2). These include measures/indicators of: service contexts (e.g., numbers of youth in the catchment area); service users (e.g., number of males accessing services); service provision/processes (e.g., portals of entry available, types of early identification strategies deployed, etc.); and outcomes/impacts (e.g., time between help-seeking and initial evaluation, satisfaction with services, reduction in distress, etc.).

**Table 2 Tab2:** Summary of assessment tools selected for the study

Instrument	Informant(s)	Key construct	Subscales	Measurement time(s)^a^
*Description of participant sample*				
Customized ACCESS OM sociodemographic questionnaire	Youth; Clinician; Administrative records	Sociodemographic characteristics	None	Intake, Months 3, 6, 9, 12 and 34/end of services
Custom checklist	Youth, Clinician	Presenting concerns	None	Intake
GAIN-SS^x^	Clinician-administered youth report	Clinical symptoms	Internalising problems, externalizing problems, substance use disorders, crime/violence	Intake, Months 3, 12 and 24/end of services
Columbia-Suicide Severity Rating Scale (C-SSRS): Screener^x^	Clinician	Suicidal ideation and behavior over past month plus one item re past suicidal behavior	None	Intake, Months 1, 3, 6, 9, 12 and 24/end of services
*Service-level improvements*				
Customized services forms	Clinician; Administrative records	Number of referrals (Hyp. 1); Number offered evaluation 72 h after referral request (Hyp 2); Number offered appropriate treatment within 30 days after completion of initial evaluation (Hyp. 3)	None	Intake, Month 1; Services forms repeated at months 1, 3, 6, 9, 12, and 24 or at end of services to document services needed and offered
CCHS-MH 2012 questions related to services sought and received	Clinician-interview with youth and/or family/carer, plus any available records	Number of help-seeking contacts made for problems with mental health/substance use and whether or not services were received in previous 12 months (Hyp. 4)	None; can examine type of contacts (formal, informal, etc.)	Intake
*Clinical improvements*				
Kessler-10 Psychological Distress Scale (K-10)	Youth	Unidimensional factor of distress as being linked to mental ill-health and varied diagnoses (Hyp. 5)	Cut-offs based on overall score (e.g., mild distress)	Intake, Months 1, 3, 6, 9, and 12
Clinical Global Impression of Severity (CGI)^x^	Clinician	Clinician’s rating of severity of youth’s presenting problem over time (Hyp. 5)	None	Intake, Months 1, 3, 6, 9, 12 and 24/end of services
Self-rated health and self-rated mental health (SRH-MH)	Youth	Self-assessment of health and mental health, each on a single 5-item Likert scale (Hyp. 5)	None	Intake, Months 1, 3, 6, 9, and 12
*Functional improvements*				
Social and Occupational Functioning Assessment Scale (SOFAS)^x^	Clinician	Social and vocational functioning on a 0 to 100 scale (Hyp. 5)	None	Intake, Months 1, 3, 6, 9, 12 and 24/end of services
*Subjective/Well-being improvements*				
Goals tool inspired by the Goals-based Outcome (GBO) tool*^x^	Youth	Self-rated progress on 3 chosen goals (Hyp. 5)	None	Intake, Months 3, 6, 12 and 24/end of services
Outcome Rating Scale (ORS)^x^	Youth	Overall outcome/ functioning/ well-being (Hyp. 5)	None; Items related to overall; individual; interpersonal; and social outcomes can be examined separately	Intake, Months 6, 12 and 24/end of services
World Health Organisation Quality of Life – Brief (WHOQOL)*	Youth	Self-assessment of quality of life (Hyp.5)	Four domains: physical health, psychological health, social relationships, and environment	Intake, Months 6, 12 and 24/end of services
*Service experiences*				
OPOC^x^	Youth, family	Satisfaction (Hyp. 6)	Access to service, services provided, participation/ rights, therapists/support workers/staff, environment, discharge, recovery outcome, service quality	Months 1, 3, 6, 9, 12 and 24/end of services
Session Rating Scale (SRS)^x^	Youth	Working Alliance (Hyp. 6)	None; Items related to relationship; goals or topic; approach or method; and overall can be examined separately	Intake, Months 6, 12 and 24/end of services
Youth Efficacy/Empowerment Scale (YES)*	Youth	Empowerment	Self, services, system	Intake, Months 3, 6, 9, 12 and 24/end of services

Hyp. = Hypothesis; OPOC = Ontario Perception of Care tool; GAIN-SS = Global Appraisal of Individual Needs –Short Screener

*Completed at select sites and not all ACCESS Open Minds sites

^a^As youth presenting with different concerns may need varying lengths of follow-up, the assessment protocol is accordingly applied. For example, if the young person receives a follow-up at an ACCESS Open Minds site for 6 months, the SOFAS will be administered at Intake, Month 1, Month 3 and Month 6. However, if they receive follow-up for just 1 month, the SOFAS will only be administered at Intake and Month 1

^X^Irrespective of length of follow-up, the following measures are to be administered at the end of follow-up: Demographic Information; SRS; YES; OPOC; WHOQOL; Services Form; SOFAS; CGI; C-SSRS; GAIN-SS; GBO-inspired tool

Measures/indicators were selected based on the following priorities:
Sustainability, to increase the likelihood of the protocol’s continued use after the research project, consistent with the ideal of measurement-based care [41–43].Wide applicability, so that measures/indicators address research objectives; inform treatment and quality improvement; and enjoy buy-in, especially from sites that had little prior research or evaluation experience. To ensure wide applicability, we chose measures/indicators targeting multiple informants, including youth, families/carers, and clinicians/service providers.Appropriateness, to choose measures shown to have adequate psychometric properties in varied Canadian youth populations. Some measures were chosen because they had been used in population-wide surveys (Canadian Community Health Survey-Mental Health [44] and Aboriginal People’s Survey [45]. This will allow the comparison of data from our sites with corresponding population-level data. When several options were available, shorter, more user-friendly measures were chosen to enhance feasibility and acceptability.

Data are collected throughout the study period, and over-time comparisons will be conducted at the network and individual site levels. At some sites, we will also conduct pre-post comparisons.

*Stepped-wedge trial*: Six sites were selected to participate in a randomized stepped-wedge trial [46, 47] wherein the intervention (a transformed service) was sequentially rolled out in three clusters/waves, starting six months apart. Sites were rank-ordered based on population, and the first three ranked sites were grouped as high and the last three ranked sites were grouped as low population. Thus stratifying by population size, two sites, one high-population and one low-population, were randomly assigned to each wave (see Fig. 1). At an event attended by representatives from all six sites, the randomization assignment was conducted by drawing chits from separate urns containing names of large and small sites (see Fig. 2).

**Fig. 1 Fig1:**
[figure not shown]
Flowchart of trial using SPIRIT flowchart recommendations

**Fig. 2 Fig2:**
[figure not shown]
Configuration of waves after randomization in April 2015

All stakeholders deemed the stepped-wedge design preferable on ethical grounds because it deployed the transformation at all sites, rather than having some sites serve solely as “controls.” For their capacity to generate high-impact evidence (like traditional RCTs), stepped-wedge trials are increasingly used to evaluate complex service-based and public health interventions [48]. They involve the random and sequential crossover of waves from the control condition to the intervention until all waves are exposed.

The lack of concealment of the allocation of the intervention can introduce selection biases to stepped-wedge trials [49–51]. It may also be difficult to separate the effects of the intervention from changes that simply happen over time. However, this can be countered statistically [52]. Such trials are prone to logistical constraints, particularly with complex, multi-component interventions [49–51]. For instance, the intervention may commence or attain adequacy at a site later than when its cluster was randomized to begin the intervention due to external events.

Per the stepped-wedge design, data collection continues throughout the study at all sites, so that each cluster contributes observations under both control and intervention conditions. All six sites thus act as controls whilst also undergoing transformation. Refer to Additional file 1: SPIRIT Checklist [53, 54], which lists where specific trial details can be found in this paper.

### Project management and participation plan

Our earlier publication [30] outlines the project’s governance structure and processes. Research is guided by a Research Advisory Group comprising representatives from all sites; network-level youth and family/carers council representatives; and network-level researchers. Overall guidance is provided by a Steering Committee of four external researchers who, together, have expertise in youth mental health, primary healthcare, Indigenous issues, and biostatistics.

At each site, evaluations are conducted by local staff, who were trained by the Montréal-based central office team, tasked with supporting sites and operationalizing the project. Site staff also receive booster training and ongoing support. At regular sessions where all sites participate, multiple raters rate the same scenarios independently on two clinician-administered measures (see Table 2), discuss ratings, and establish consensus guided by experts. These sessions help raters calibrate themselves in relation to a scale’s anchors and ensure that scales are reliably rated across sites.

Videos [55–57] were created to explain the project, the role of evaluations, and informed consent to site staff and youth. Videos featuring actors were also developed to demonstrate best practices for introducing evaluations and informed consent to youth. The project’s national youth council created and shared engaging, youth-friendly posters describing the project and its research/evaluation strategy.

### Participant recruitment, consent and withdrawal

The sites will recruit youth for a period of 3–3.5 years until September 2020. The first participant was enrolled in the study in July 2016. Participants include youth and, where possible, their families/carers.

While details vary across sites, the general recruitment procedure is for the ACCESS Clinician or another staff member to identify new referrals to a research assistant/staff who explains the project to them and seeks written informed consent (see Additional file 2 for sample consent form). Consenting youth are enrolled into the study.

The protocol recommends approaching youth for written consent at the time of intake. However, recruitment can be deferred if youth are in crisis situations or too busy. For minors below the age of 14 or youth with diminished capacity, consent is sought from a parent/legal representative along with assent from the young person. Provincial/institutional regulations vary in terms of policy around the need for consent from a parent/legal representative in the case of youth between the ages of 14 and 18 (see Declaration about “Ethics approval and consent to participate”).

Consent is also sought from family members for their participation in family-focused assessments. Signed forms are filed securely in locked cabinets and copies are given to participants.

Consent is voluntary and can be withdrawn at any time, with no impact on access to services or the quality of care. Consent simply allows data from measures completed by youth and from their health administrative records to be recorded and analyzed for the research project.

Following youth feedback, a consent form (see Additional file 2) was created that, while modeled on standard ethics guidelines, minimized length and legalese. It describes the services offered, details the research/evaluation component, and clarifies that consenting to research is not a prerequisite to receiving services. It thus respects the project’s philosophy of integrating care and evaluations. Across sites, the wording or structure of consent forms varies to respect local ethics procedures and cultural considerations. Sites have also developed recruitment strategies suited to their context and youth population. Some sites offer honoraria/compensation to youth for time and travel costs incurred in completing assessments, and others often meet youth outside, in the community or a café, to complete assessments, etc.

*Inclusion and exclusion criteria*: To recruit as representative a sample as possible of *all* youth served, inclusion criteria are broad and exclusion criteria minimized. For enrollment into research/evaluation, youth must be aged 11 to 25 years and be seeking help for a mental health and/or substance-related problem. Youth who received services at a site before its transformation are eligible if they have not received any services for six months or longer. This was done to ensure that the study of outcomes is restricted to those receiving transformed services. Individuals younger than 11 years or older than 25 years; with a diagnosed intellectual disability; with a history of organic brain damage; and/or deemed unable to consent are not eligible. For family members/carers to be included in the research, they must be connected to a youth receiving services at a site and provide informed consent.

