### Secondary objectives

To determine if the ACCESS Open Minds model:
4.Simplifies pathways to mental healthcareHypothesis 4: Over the course of the project, youth will make fewer help-seeking contacts in the previous 12 months before accessing services at project sites.5.Improves outcomes for youth served at project sitesHypothesis 5: The clinical, social-vocational and subjective functioning of youth will significantly improve over the course of their follow-up. An additional objective is to determine which outcome domains are most impacted by treatment. The lengths of follow-up will vary depending on youth’s needs, severity of illness, etc.6.Satisfies youth and their familiesHypothesis 6: At least 75% of service users and their families/carers will be satisfied with services and service providers at all completion time-points.

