### Outcome measures

Outcome measures are summarized in Table 2 and their psychometric properties in Additional file 3. Measures that were available only in English were translated into French with forward and back translation and a focus on conceptual equivalence [58, 59]. All purpose-designed forms are available in English and French. Measures of clinical, functional and subjective outcomes are administered at baseline and repeated for those who receive further treatment.

*Sample description*: Socio-demographic variables like sex, age, housing situation, ethnicity, and immigration background are obtained from a self-report form, clinical interviews, or records. Such data are crucial given the known social determinants of mental healthcare access and outcomes.

Where possible, items were picked to allow population-level comparisons, e.g., a Canadian census indicator of visible minority status [60] to help determine whether sites serve as many minority youth as the ethnic composition of their catchment populations would suggest they should.

A clinical profile of service recipients is created using a purpose-designed checklist of presenting concerns, the Global Assessment of Individual Needs-Short Screener [61], and the Columbia-Suicide Severity Rating Scale screener [62], among other tools..

*Service-level outcomes*: Forms were purpose-designed to record information about sites’ performance on key indicators pertaining to our three main hypotheses (increase in number of youth assessed, evaluation within 72 h, and adherence to the 30-day benchmark).

Data from these forms will also help identify barriers to meeting project benchmarks (e.g., delay due to lack of an on-site psychiatrist) and site-level quality improvement (e.g., information on referral sources will help tailor early case identification activities). Secondary questions can also be asked, e.g., about whether self-referrals increase over the course of the project. Staff will record on these forms up to three services needed by youth following the initial evaluation and services received by them 30 days later, which will serve as our measure of “appropriate” care.

Items taken from the Canadian Community Health Survey-Mental Health (CCHS-MH) 2012 survey [44] are used to determine whether youth are first-time help-seekers and the number and types of help-seeking contacts they make before entering a site (Hypothesis 4).

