### Statistical plan

Every attempt will be made to collect outcome data from all participants, including those who do not complete treatment. Youth will be considered as having a serious mental illness if they attain the relevant scale-specific cut-off scores on the K-10, SOFAS and/or the CGI-severity scale.

*Pre-post minimum evaluation protocol*: For each site, general linear models with repeated measures will be used to analyze differences over time per site (for hypotheses pertaining to increased referrals, evaluations within 72 h, treatment within 30 days, number of prior help-seeking contacts, and satisfaction with services) and per youth (at baseline and at follow-up timepoints for the hypothesis pertaining to improvements in functioning). Generalized estimation equations will be employed for parameter estimation. Respective baseline values will be added to the model as a covariate. Additional analyses will include examining hypothesis 3 separately for youth with and without serious mental illnesses, examining inter-site heterogeneity, and identifying baseline predictors of response to treatment. Finally, outcomes will be examined separately for large urban, small urban/rural and Indigenous contexts.

*Trial*: Youth demographics and clinical data will be described using means and standard deviations and trial waves will be compared using t-tests or non-parametric tests for quantitative characteristics. The effect of the interventions on the three primary and all secondary outcomes will be quantified using mixed or multi-level models to integrate cluster/wave and time effect. The unidirectional crossover design of the stepped-wedge trial allows us to test the effect of the intervention at both within- and between-cluster levels. Mixed models allow stratification (e.g., by population sizes); inclusion of missing data with the principle of intention to treat; and adjustment for baseline differences.

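### Hypothesis 4 looks back 12 months but former clients may enrol after six, so a site's own pre-transformation care can enter the count only among early entrants: a possible time-dependent bias of unknown size

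*Protocol article*

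**What the plan says.** All references are to the protocol article.

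- **Re-entry rule** (Participant recruitment, consent and withdrawal; inclusion and exclusion criteria): "Youth who received services at a site before its transformation are eligible if they have not received any services for six months or longer". The reason given is: "This was done to ensure that the study of outcomes is restricted to those receiving transformed services". Pathways to care are not mentioned.
- **H4** (Secondary objectives): "Over the course of the project, youth will make fewer help-seeking contacts in the previous 12 months before accessing services at project sites".
- **Measurement** (Table 2, at intake only): "Number of help-seeking contacts made for problems with mental health/substance use and whether or not services were received in previous 12 months (Hyp. 4". The same row says of subscales: "None; can examine type of contacts (formal, informal, etc". An own-site category is not mentioned.
- **Second description of the measure** (Outcome measures): "the number and types of help-seeking contacts they make before entering a site (Hypothesis 4".
- **Analysis** (Statistical plan): "number of prior help-seeking contacts, and satisfaction with services" are among the items modelled as differences over time per site. The stepped-wedge mixed models also cover all secondary outcomes.

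**The concern.** The two windows differ by six months. A youth whose last visit to the site was, say, nine months ago satisfies the re-entry rule, and that visit lies inside the H4 look-back. If it is counted, care already received at the site is recorded as part of the pathway to the site.

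A constant error of this kind would matter little for a trend. This one is not constant. Care given before the transformation moves out of the look-back as time since the transformation passes, and from month 12 none of it can remain. H4 predicts a fall over the course of the project, so a component that fades on the same time axis could be mistaken for simpler pathways. Because it follows time since transformation, an adjustment for calendar time alone would not be sure to remove it.

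H4 is a secondary hypothesis. The primary hypotheses are not touched.

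**Working it through.** **The plan's own figures.** The article gives no expected value or effect for H4. Its one sample-size figure is consistent: the 14 site targets in Table 1 and its footnote add up to 3616, and 6029 × 0.60 = 3617.4. That figure is not affected by this point.

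**Inputs from the article.** Service-free interval: at least 6 months. Look-back: 12 months. Recruitment: 3 to 3.5 years, i.e. 36 to 42 months.

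**Step 1: when the overlap can occur.** Let a youth enter *t* months after the site's transformation, with the last pre-transformation service *s* ≥ 0 months before it. The gap is *t + s*, which cannot be less than *t*. The youth is eligible if the gap is at least 6, and that service lies in the look-back if the gap is below 12. The range of gaps meeting both conditions is

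width = max(0, 12 − max(6, *t*)).

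| Entry month *t* | 0 | 3 | 6 | 8 | 9 | 10 | 11 | 12 or later |
|---|---|---|---|---|---|---|---|---|
| Width (months) | 6 | 6 | 6 | 4 | 3 | 2 | 1 | 0 |

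This is a range of gaps, not a share of youth. If recruitment starts at the transformation, the exposed first 12 months are 12/42 = 29% to 12/36 = 33% of recruitment time.

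**Step 2: size, on assumed inputs.** None of the following is in the article. Let *f* be the share of early entrants who are former clients with a gap of 6 to 12 months (2% to 20%), *c* their own-site contacts in the window (1 to 3), and *m* the mean number of other contacts per 12 months (1 to 6). Own-site care is taken as counted.

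- *The rule means services at this site only:* shift in the early mean = *f × c*. Lowest: 0.02 × 1 = 0.02. Highest: 0.20 × 3 = 0.60. Middle case: 0.10 × 2 = 0.20, which is 5% of *m* = 4.
- *The rule means services anywhere:* former clients also lack service contacts in the latest half of the look-back. With other contacts spread evenly and none in that half, shift = *f × (c − m/2)*. Lowest: 0.20 × (1 − 3) = −0.40. Highest: 0.20 × (3 − 0.5) = +0.50. With *f* = 0.10, *c* = 2, *m* = 4 it is 0.

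**Step 3: a second set of assumptions, site-only reading.** Let the gap be 6 months plus an exponential with mean 9. The share of returners with own-site care in the window is then:

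- entry in months 0 to 6: 1 − exp(−6/9) = 49%;
- entry in months 6 to 12, among those whose gap is at least *t*: [9(1 − e^(−2/3)) − 6e^(−2/3)] / [9(1 − e^(−2/3))] = (4.38 − 3.08)/4.38 = 30%;
- pre-transformation care, entry from month 12: 0%.

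If returners are 10% to 30% of entrants, the excess in months 0 to 6 over month 12 onward is 0.49 × 0.10 = 0.05 to 0.49 × 0.30 = 0.15 when an earlier episode counts as one contact. With earlier episodes lasting 4 months on average (exponential), a returner brings 1.02 contacts at one visit a month and 2.03 at two. The excess is then 0.10 to 0.31, or 0.20 to 0.61.

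**Step 4: after the change.** With own-site contacts left out, or with the H4 analysis set limited to youth without care at the site in the previous 12 months, the overlap is 0 at every entry date.

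**The case against.** A reader might infer that H4 must fall by construction and that the bias necessarily favours confirming it. The documents do not support that, for five reasons.

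1. **Own-site care may not be counted.** The hypothesis speaks of contacts "youth will make fewer help-seeking contacts in the previous 12 months before accessing services at project sites", and the Outcome measures section of contacts made before entry to a site. Both can be read as leaving out the site itself. Only the Table 2 row lacks such wording. The data form or full protocol may settle the matter. This stands as an ambiguity: neither phrase says whether first-ever or current entry is meant.
2. **The sign depends on the scope of the six-month rule**, which does not say whether it covers services at that site or anywhere. This stands; see Step 2.
3. **The control periods are not characterised.** The stepped-wedge models contrast control and intervention periods. Inflated counts just after the switch fall in the intervention condition and would work against H4 there, unless control-period counts are inflated at least as much. The article gives nothing from which to determine this.
4. **Own-site contacts need not vanish after month 12.** That holds for pre-transformation care only. The article expects about 60% of youth approached to consent. Some of the other 40% could return and enrol later, bringing post-transformation contacts at the site with them.
5. **The size rests wholly on assumptions.** Returner share, gaps, visit rates and mean contacts are not given.

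It can also be said that a counting rule is an analysis detail. That does not dispose of the point: both windows are fixed in the article and do not match, and the stated reason for the six-month rule concerns outcomes, not pathways.

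**Conclusion.** The point holds as a possible time-dependent bias in one secondary hypothesis. What the text establishes is that the six-month interval is shorter than the 12-month look-back, that own-site care is not clearly excluded, and that pre-transformation care at the site can enter the count only for intakes less than 12 months after the transformation.

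Direction is conditional. For the over-time analysis, the bias favours H4 if the rule concerns that site only and own-site care is counted. If the rule covers services anywhere, the sign is open. For the control-versus-intervention contrast the direction cannot be determined from the article.

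Size is unknown. The ranges of 0.02 to 0.60 and −0.40 to +0.50 contacts show what the assumed inputs would produce; they are not estimates for this trial. With few returning youth the effect is negligible.

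**What to change.** Either of two changes to the H4 analysis is enough:

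- **Align the analysis set.** Analyse H4 in youth with no service at that site, before or after the transformation, in the 12 months before intake. To apply the six-month rule, a site must already know when a former client was last served, so the same records identify these youth.
- **Separate the contacts.** Record own-site contacts as their own category and leave them out of the H4 count. Table 2 mentions formal and informal types only, so first confirm that own-site contacts can be identified, for example from the records that Table 2 allows as a source.

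In both cases, apply the same rule in control and transformed periods, and state whether the six-month rule refers to services at that site or anywhere. Eligibility for the study need not change.

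The cost is that some returning youth, or some of their contacts, drop out of this one secondary analysis. No added recruitment is needed, and the primary analyses stay as they are.
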